## Methods/design

### Study design

The study is a double-blind, randomised, crossover, controlled trial that will randomise 120 hypertensive subjects to 12 weeks treatment with spironolactone 50 mg once daily and 12 weeks treatment with bendroflumethiazide 2.5 mg once daily. The 2 treatment periods are separated by a 2-week washout period. Investigators and subjects do not know the order of the treatment periods, which is according to a computer generated randomisation list. Randomisation is stratified by aldosterone: renin ratio to include equal numbers of subjects with high and low aldosterone: renin ratios. This is necessary as in an unselected population, only 15% of subjects will have an aldosterone: renin ratio > 750.

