#### Secondary endpoints

Secondary endpoints include the differences between the following measurements taken at the end of each 12-week treatment period

• Mean 24 hour diastolic ambulatory blood pressure

• Mean daytime ambulatory blood pressure

• Mean night time ambulatory blood pressure

• Mean clinic blood pressure defined as mean of mean clinic BPs on both penultimate and final days of treatment periods

• Clinical biochemistry measurements of plasma potassium (K^+^), magnesium (Mg^2+^), creatinine, triglycerides, cholesterol and HDL cholesterol

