#### Analyses

For each outcome the measurement from the spironolactone treatment period will be subtracted from that of the bendroflumethiazide treatment period. Therefore each person has an estimated "treatment effect". The mean difference, between the treatment effects in the high ratio group and those in the low ratio group, will be compared by t-tests and 95% confidence intervals. There may be some secondary Normal Linear Models that also examine other factors, which may also be considered to be confounders, as this is a non-randomised comparison.

The second analysis will be by conventional crossover analyses of the efficacy of spironolactone (in the high-ratio sub-group only). These analyses will be carried out by Normal Linear Models, that include parameters for patient, period and treatment. In the event that a variable is not normally distributed then the within-patient treatment differences will be calculated and then analysed by either t-tests or Wilcoxon tests.

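### The non-normality fallback for the high-ratio crossover analysis drops the period term, and its t-test option gives no added protection against non-normality

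*Protocol article*

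**What the plan says.** The Analyses section of the protocol article plans two analyses. The first compares each patient's drug difference between the high-ratio and low-ratio strata by t-tests. The second is a crossover comparison of the two drugs within the high-ratio stratum only, and for it the article says: "These analyses will be carried out by Normal Linear Models, that include parameters for patient, period and treatment".

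The same paragraph then gives a contingency: "In the event that a variable is not normally distributed then the within-patient treatment differences will be calculated and then analysed by either t-tests". The sentence does not end there. The differences are to be "analysed by either t-tests or Wilcoxon tests". Neither test is given a period adjustment.

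Under Study design, "The 2 treatment periods are separated by a 2-week washout period", and staff and subjects are blind to "the order of the treatment periods, which is according to a computer generated randomisation list". The article does not say how evenly the two sequences will fall within each stratum. The secondary endpoints include "creatinine, triglycerides, cholesterol and HDL cholesterol", positive quantities for which the contingency could plausibly be invoked.

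**The concern.** The contingency is meant to protect the crossover analysis when normality fails. Three features work against that.

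- **The trigger looks at the wrong quantity.** It asks whether a variable is normal. The model needs normality only of the within-patient errors, because the patient term absorbs the differences between patients. A variable can be skewed across patients and still satisfy the model, and the reverse can also happen.
- **The t-test option is not a remedy.** It makes the same assumption about the same errors as the model it replaces.
- **Both options, as written, omit period.** The planned model includes it. Without it, any period effect adds to the spread of the treatment differences. If the sequences are unequal in size, it also shifts their mean.

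At stake are some power, and possibly some bias, in the treatment comparison within the high-ratio stratum, for those outcomes that trigger the rule.

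**Working it through.** **1. Inputs from the plan.** The section on power and sample size gives an SD of 11 mmHg, a difference of 6 mmHg, 80% power, two-sided α of 0.05, and 28 (within stratum) or 54 (between strata) patients per stratum. These reproduce if 11 is the SD of the within-patient difference:

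- Within stratum: (1.960 + 0.842)² × 11²/6² = 26.4, so 27 by the normal approximation. The t-based solution is 28.4, and power at 28 is 79.5%.
- Between strata: twice 26.4 is 52.8, so 53. The t-based solution is 53.7, and power at 54 is 80.2%.

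So n = 54 and a difference SD of 11 are used below. Period effects, sequence splits and log-scale parameters are not in the article and are assumptions.

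**2. What the planned model tests.** Let τ be the treatment difference, π the period difference (period 1 minus period 2) and e the difference of a patient's two errors. The patient term cancels on subtraction:

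- Period difference: π + τ + e in one sequence, π − τ + e in the other. The model tests τ by comparing these between sequences, which is a two-sample t-test.
- Treatment difference: τ + π + e in one sequence, τ − π + e in the other. A paired t-test takes their overall mean and ignores the ±π.

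Normality is required of e in both cases. On one simulated data set the planned model and the two-sample t-test on period differences agree exactly (t = −3.344, p = 0.00154). The model without period and the paired t-test also agree exactly (t = −3.283).

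**3. Cost of dropping period, normal errors, assumed π = 6 mmHg.**

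*Balanced sequences, 27:27.* No bias, but the SD of the differences becomes √(11² + 6² × 54/53) = 12.56. The estimated standard error is 12.56/√54 = 1.709, against a true value of 11/√54 = 1.497. The critical difference is 2.006 × 1.709 = 3.43. For a true 4 mmHg effect, power is about Φ((4 − 3.43)/1.497) = 65%. With period in the model the critical difference is about 2.006 × 1.497 = 3.00, and power is about Φ((4 − 3.00)/1.497) = 75%. Simulation (3000 runs) gives 65.0% and 75.0%. Type I error of the paired t-test is 2.6%.

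*Unbalanced sequences, 32:22.* Bias = 6 × (32 − 22)/54 = 1.11 mmHg. Simulated type I error is 7.3% (paired t) and 6.9% (signed-rank), against 5.4% for the model and 5.0% for a rank-sum test on period differences between sequences.

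*Smaller period effect.* With π = 3 mmHg at 32:22, the bias is 3 × 10/54 = 0.56 mmHg. The SD is √(121 + 9 × (1 − (10/54)²) × 54/53) = 11.40 and the critical difference is 2.006 × 11.40/√54 = 3.11. Type I error is about P(Z > (3.11 − 0.56)/1.497) + P(Z < (−3.11 − 0.56)/1.497) = 4.4% + 0.7% = 5.1%. This normal approximation runs slightly low. The inflation therefore needs both a sizeable period effect and a clear imbalance.

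**4. Skewed outcomes.** Assumed log-normal data, n = 54, within-patient correlation 0.6, 4000 runs. Power in %:

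| Log-SD, drug effect, period effect | Planned model, raw scale | Paired t | Signed-rank | Same model on logs |
|---|---|---|---|---|
| 0.5, 15%, none | 53.6 | 53.6 | 56.0 | 61.7 |
| 0.7, 25%, none | 58.3 | 58.3 | 65.4 | 73.0 |
| 0.5, 20%, 20% | 74.4 | 70.0 | 72.8 | 83.2 |

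In the last setting the rank-sum test between sequences has 76.6%. The losses against the planned model are 74.4 − 70.0 = 4.4 points (t-test) and 74.4 − 72.8 = 1.6 points (signed-rank). A second run of that setting (5000 trials, 27:27) gives 74.1, 70.1 and 72.8, so 4.0 and 1.3 points.

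**5. Heavy tails.** With t-distributed errors (3 df, SD 11), a 4 mmHg effect and no period effect, signed-rank has 93% power against 80% for the model and the paired t-test. With a 6 mmHg period effect, signed-rank falls to 81%, level with the model (81%). Paired t has 72% and the rank-sum test between sequences 93%.

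**The case against.** A reader might infer that the fallback cures nothing. The text does not support that. The sentence offers Wilcoxon tests as well as t-tests, and these do relieve non-normality: 65.4% against 58.3% in the more skewed setting above, and 93% against 80% under heavy tails.

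A reader might also infer that the test will be picked after the results are seen. Always taking the smaller p-value would give a type I error of about 6% to 7%, but nothing in the article says this will be done. A rule for choosing is detail that an analysis plan not shown here may hold, so it forms no part of the point.

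The sentence can be read charitably as a sequence: compute differences, use a t-test if they look normal and a Wilcoxon test if not. That is sensible as far as it goes. But if the differences are normal the planned model was already valid, so leaving it gains nothing and loses period. More charitably still, the tests might be meant to compare sequences, as in the classical crossover t-test. The wording speaks of treatment differences and does not say so. On that reading the period concern falls away, but the t-test is then numerically the planned model itself.

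Two points against a larger claim stand. First, most of the advantage of the log-scale model comes from the scale and not from keeping period: 83.2 − 74.4 = 8.8 points separate it from the planned raw-scale model, and the data were simulated as log-normal. Second, nothing in the article suggests that 24-hour systolic pressure would trigger the rule, and the article does not describe any listed outcome as skewed.

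**Conclusion.** The point holds as a limited correction to a stated rule. The t-test option is redundant as a remedy for non-normality; with complete two-period data this is an algebraic identity and needs no assumption. The Wilcoxon option is a genuine remedy, but as written it shares the loss of the period term. The trigger should concern residuals.

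The size depends on assumptions. With balanced sequences and a 20% period effect on skewed data, the loss is about 4 points of power for the t-test and 1 to 2 for signed-rank. With normal errors and a 6 mmHg period effect it is about 10 points for the t-test. At an assumed 32:22 split and 6 mmHg, bias is 1.1 mmHg and type I error about 7%; at 3 mmHg the error is close to nominal. Without a period effect, nothing is lost by omitting the term.

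The impact is confined to the second analysis and to outcomes that prove non-normal. The t-test between strata and the sample size do not depend on this sentence.

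**What to change.** Replace the contingency sentence with wording to this effect:

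> Distributional assumptions are checked on the residuals of the patient-period-treatment model. Positive outcomes with skewed residuals are analysed as logarithms in the same model and reported as ratios. If residuals remain clearly non-normal, the period 1 minus period 2 differences are compared between the two sequences by the Wilcoxon rank-sum test.

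Delete the t-test option. The rank-sum test keeps the period adjustment and costs almost nothing when there is no period effect: 55.5% power against 55.8% for signed-rank in the 15% setting (5000 trials).

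The cost is one sentence. The downside is that log-scale outcomes are reported as ratios and not as absolute differences. No change in sample size or data collection is needed.

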## Substudies

The reason for these sub-studies is that the indices measured (QT dispersion, heart rate variability, endothelial function and exercise BP) are considered reasonably good surrogates for future cardiovascular events and mortality [19-21] Certainly, in the case of chronic heart failure, the spironolactone-induced improvement in mortality in Randomised Aldactone Evaluation Study (RALES) [22] was paralleled by spironolactone induced improvements in QT dispersion, heart rate variability[23] and endothelial function[24]. The results of these substudies may be useful indicators of future cardiovascular outcomes.

### QT dispersion

QT dispersion is measured from routine ECGs recorded at baseline and at the end of each treatment period. Spironolactone has been shown to reduce QT dispersion in chronic heart failure[23] and it is of interest to investigate whether this is also the case in hypertension and whether such an effect is more prominent in subjects with a high aldosterone: renin ratio.

### Heart rate variability

Heart rate variability is assessed from 24-hour ambulatory ECG monitoring carried out at the end of each treatment phase. Again, spironolactone has been shown to improve the parasympathetic component of heart rate variability[23] and it is of interest to examine if this is also the case in hypertension and whether such an effect is more prominent in subjects with a high aldosterone: renin ratio. Ventricular ectopic activity on the 24 hr tapes is also measured.

### Endothelial function

A subset of the subjects undergoes endothelial function assessment by a standard protocol. At the end of each treatment period, these subjects undergo a detailed brachial artery infusion study with sequential infusions of acetylcholine, nitroprusside and LNMMA (NG-monomethyl-L-arginine) combined. In CHF, spironolactone improves endothelial function[24] even in the presence of an ACE inhibitor. It will therefore be of major interest to see the effect of spironolactone in hypertension and whether such an effect is more prominent in subjects with a high aldosterone: renin ratio.

### Pulsewave analysis and velocity

In parallel with the detailed invasive assessment of endothelial function described above, a larger cohort of each sub-group undergoes a non-invasive measurement of vascular compliance and pulse waveform characteristics using the Sphygmocor technique. This measurement is likely to be influenced by the baseline ratio, and for this reason balanced numbers of subjects in each subset are recruited. This measurement will be made at the end of each treatment period.

### Exercise blood pressure

All subjects also have their blood pressure measured after a 3-minute exercise step-test, The Dundee Step Test. Preliminary data suggests that exercise BP is correlated with the aldosterone: renin ratio[25].

### Plasma and urinary steroids

A blood sample for plasma steroids is taken at baseline. A 24 h urine collection is also done and will be analysed for electrolytes, aldosterone and urinary steroids including 18-oxocortisol. These data will be used to investigate if there are any predictors of the BP response that are superior to the aldosterone: renin ratio.

### Plasma PIIINP (Procollagen Type III N-terminal Peptide)

Plasma PIIINP is a marker for collagen formation in the heart and spironolactone has been found to reduce PIIINP in heart failure[26]. We wish to examine whether if this is also the case in hypertension.

### DNA

A blood sample is drawn to assess the effect of polymorphic variation at the aldosterone synthase (CYP11B2) gene (SF1, 344T/C and intron 2 conversion) on baseline phenotypic abnormalities and response to therapy. In addition, all subjects are screened for the gene for glucocorticoid remediable aldosteronism (GRA).

### Ethical approval

The main study and sub-studies have ethical approval from Tayside Committee on Medical Research Ethics and West Ethics Committee, Western Infirmary, Glasgow.

## Discussion

The numerous deleterious effects of hypertension[27] dictate the need for a systematic approach for its treatment. In spite of various therapies, resistant hypertension is widely prevalent [28]. Among various factors, primary aldosteronism is an important cause of resistant hypertension and is now more commonly recognised[4,5,29]. Moreover even in treated hypertensives, the mortality remains up to five times higher compared to normotensives[30]. One of the factors might be inadequate blood pressure control due to usage of inappropriate drugs. More significantly, hypertensives with primary aldosteronism are also exposed to various other deleterious effects of excess aldosterone [31]. Aldosterone has deleterious effects on the myocardium and induces myocardial hypertrophy, fibrosis and necrosis[32,33]. Aldosterone is implicated in heart failure and its blockade in significantly reduces mortality[22,34]. Aldosterone also induces endothelial dysfunction[35]. Hence treating hypertension with specific aldosterone antagonists may be a better approach in this group of patients. It may lead on to better blood pressures with fewer medications[16].

